## **STUDY SUMMARY IN LOCAL LANGUAGE**

### **GERMAN**

Nach derzeitigen Empfehlungen wird für die Einleitung und Erhaltung der antiretroviralen Therapie eine Kombination von drei Medikamenten angeboten. Vereinfachungen der Therapie und der Pflege werden in Bezug auf eine verbesserte Patientenbindung sowie reduzierte Gesundheitskosten als kritisch betrachtet. Aktuell werden vereinfachte Erhaltungstherapien selten eingesetzt und basieren meist auf verstärkten Protease-Inhibitoren oder Dual-Therapien.

Dolutegravir ist ein Integrase-Inhibitor, mit ausgezeichneter Toleranz, sehr guter Wirksamkeit, wenig Wechselwirkungen mit anderen Medikamenten und einer hohen genetischen Resistenzbarriere in kombinierter Therapie. Diese Eigenschaften deuten darauf hin, dass Dolutegravir eine akzeptable und wirksame Alternative als vereinfachte Erhaltungstherapie sein könnte (mit nukleosidischer Reverse-Transkriptase-Inhibitoren).

Dies ist eine multizentrische klinische Studie, welche die Wirksamkeit von Dolutegravir und Emtricitabine in Dual-Therapie als Erhaltungstherapie bei freiwilligen, virussupprimierten Patienten untersucht. Ziel ist es aufzuzeigen, dass die Erhaltungstherapie in Bezug auf die Virussuppression nicht schlechter ist als die Standard-Dreifachtherapie, und dass vereinfachte Laborkontrollen in Bezug auf Kosten, Akzeptanz, Sicherheit und Lebensqualität für die Patientenden Standard-Kontrollen überlegen sind.

184 Teilnehmer werden aus der Schweizerischen Kohortenstudie rekrutiert. Diese Patienten haben eine nicht nachweisbare Virämie seit mindestens 24 Wochen unter herkömmlicher Dreifachtherapie und kein Therapieversagen mit Integrase-Inhibitoren in der Vergangenheit. Die Teilnehmer werden nach Zufallsprinzip eingeteilt (randomisiert) und wechseln entweder auf Dolutegravir und Emtricitabine als Dual-Therapie oder führen ihre Standard-Therapie fort; eine zweite Randomisierung teilt sie entweder der vereinfachten oder der Standard-Laborüberwachung zu. Bei allen Patienten werden während 48 Wochen die Adhärenz und die Virämie, zuerst in einem Abstand von 6 Wochen und nach dem ersten Quartal vierteljährlich kontrolliert.

Allen Patienten die Woche 48 der Studie abgeschlossen haben, können ihre Zustimmung geben, die Nachbeobachtung auf 3 Jahre mit 1 Besuch pro Jahr zu verlängern.

Diese Studie ist insofern verallgemeinerbar, da wir Patienten aus dem Netzwerk der Schweizerischen Kohorte rekrutieren. Darüberhinaus beabsichtigen wir zu zeigen, dass eine vereinfachte Erhaltungstherapie gut verträglich und auch in Regionen mit limitierten Ressourcen durchführbar sein kann.

Mit einer Nachbeobachtung von 144 Wochen, hoffen wir, die Frage nach der Wirksamkeit der Dolutegravir und Emtricitabine Dual-Therapie mit ausreichender Teststärke und annähernd dem Kontext des wirklichen Lebens beantworten zu können.

### **FRANÇAIS**

Les recommandations de traitement proposent actuellement une combinaison de trois médicaments pour l'initiation et la maintenance d'une thérapie antirétrovirale. La simplification du traitement et de son suivi est considérée comme critique pour améliorer la rétention en soins et réduire les coûts de la santé. Les traitements simplifiés de maintenance actuels sont peu utilisés et reposent sur l'utilisation d'antiprotéases boostées ou de bithérapies.

Le dolutegravir est un inhibiteur de l'intégrase, avec une excellente tolérance, une très bonne efficacité et des interactions médicamenteuses limitées, ainsi qu'une haute barrière génétique à la résistance en traitement combiné. Ces caractéristiques suggèrent que le dolutegravir pourrait être une option acceptable et efficace en traitement de maintenance simplifié (avec inhibiteur nucléosidique de la reverse transcriptase).

Il s'agit d'un essai clinique multicentrique visant à tester l'efficacité d'un traitement de maintenance par dolutegravir et emtricitabine en bithérapie chez des patients volontaires et en suppression virologique. L'objectif est de démontrer que cette thérapie de maintenance n'est pas inférieure en terme de suppression virologique, en comparaison avec une thérapie antirétrovirale standard, et qu'un suivi de traitement simplifié est bénéfique en terme de coût, d'acceptabilité, de sécurité et de qualité de vie pour les patients si on le compare au suivi standard.

184 participants seront recrutés principalement au sein de l'Etude suisse de cohorte VIH. Ces patients auront une charge virale indétectable depuis au moins 24 semaines, sous thérapie antirétrovirale conventionnelle, sans antécédent d'échec au traitement antirétroviral. Les participants seront randomisés pour recevoir soit une bithérapie de dolutegravir et emtricitabine, soit pour poursuivre leur thérapie standard; une seconde randomisation les assignera soit à un suivi décentralisé et allégé, soit à un suivi standard. Tous les patients seront vus durant 48 semaines, avec des visites fréquentes de vérification d'adhérence et de la charge virale, aux 6 semaines sur le premier trimestre puis de manière trimestrielle. Les patients ayant terminé la semaine 48 de l'étude, pourront donner leur consentement pour étendre le suivi post-étude à 3 ans avec 1 visite par année.

Cet essai se veut généralisable car nous comptons prouver qu'un traitement de maintenance simplifié pourrait être bien toléré et disponible également dans les régions à ressources limitées.

Avec un suivi étendu à 144 semaines, nous espérons répondre à la question de l'efficacité du dolutegravir et de l'emtricitabine en bithérapie avec une puissance suffisante pour nous approcher du contexte de la vie réelle.

## ITALIAN

Le raccomandazioni attuali per la terapia propongono una combinazione di tre farmaci per l'inizio e il mantenimento di una terapia antiretrovirale. La semplificazione della terapia e del follow-up è considerata critica per il mantenimento in terapia e per ridurre i costi della salute. Le attuali terapie semplificate di mantenimento sono poco utilizzate et sono basate sull'uso di antiproteasi con ritonavir o di biterapie.

Il dolutegravir è un inibitore dell'integrase con un'eccellente tollerabilità, un'efficacia molto buona, poche interazioni medicamentose nonché un'alta barriera genetica allo sviluppo di resistenze in caso di terapia combinata. Queste caratteristiche suggeriscono che il dolutegravir potrebbe essere un'opzione accettabile ed efficace nella terapia di mantenimento (con inibitore nucleosidico della transcriptasi inversa).

Si tratta di uno studio clinico multicentrico che mira a testare l'efficacia di una terapia di mantenimento con dolutegravir ed emtricitabina in biterapia in pazienti volontari in soppressione virologica. L'obiettivo è dimostrare che questa terapia semplificata di mantenimento è non inferiore, in termini di soppressione virologica, a una terapia antiretrovirale standard e che un follow-up semplificato è benefico in termini di costi, accettabilità, sicurezza et qualità di vita per i pazienti rispetto al follow-up standard.

180 partecipanti saranno reclutati principalmente all'interno dello studio svizzero della coorte. Questi pazienti avranno una carica virale indettabile da almeno 24 settimane, in terapia antiretrovirale convenzionale, senza precedenti di fallimenti della terapia antiretrovirale. I partecipanti saranno randomizzati per ricevere una biterapia di dolutegravir et emtricitabina o per proseguire la loro terapia standard; una seconda randomizzazione li assegnerà a un follow-up semplificato o a un follow-up standard. Tutti i pazienti saranno visitati alla settimana 48 con frequenti visite di verifica dell'adesione terapeutica e della carica virale ogni 6 settimane durante il primo trimestre et poi con frequenza trimestrale. Una volta finita la settimana 48 dello studio, i pazienti potranno dare il loro consenso ad estendere il periodo di monitoraggio post-studio a 3 anni con una visita all'anno.

Questo studio si vuole generalizzabile poiché noi contiamo dimostrare che una terapia di mantenimento semplificata potrebbe essere ben tollerata e disponibile anche nelle regioni con risorse limitate.

Con un follow-up della durata di 144 settimane, speriamo rispondere alla domanda relativa all'efficacia di dolutegravir ed emtricitabina in biterapia con una potenza sufficiente per avvicinarci al contesto della vita reale.

## **Abbreviations**

Provide a list of abbreviations used on the protocol

|       |                                                                                              |
|-------|----------------------------------------------------------------------------------------------|
| ACTG  | AIDS Clinical Trial Group                                                                    |
| AE    | Adverse Event                                                                                |
| ART   | Antiretroviral Therapy                                                                       |
| ASR   | Annual Safety Report                                                                         |
| CA    | Competent Authority (e.g. Swissmedic)                                                        |
| CEC   | Competent Ethics Committee                                                                   |
| CK    | Creatine Kinase                                                                              |
| CNS   | Central Nervous System                                                                       |
| CRF   | Case Report Form                                                                             |
| ClinO | Ordinance on Clinical Trials in Human Research ( in German: KlinV, in French: OClin ) |
| CRA   | Clinical Research Associate                                                                  |
| CRC   | Clinical Research Centre                                                                     |
| eCRF  | Electronic Case Report Form                                                                  |
| EDC   | Electronic Data Capture                                                                      |
| CTCAE | Common terminology criteria for adverse events                                               |
| CTU   | Clinical Research Centre                                                                     |
| DSMB  | Data Safety and Monitoring Board                                                             |
| DSUR  | Development safety update report                                                             |
| DTG   | Dolutegravir                                                                                 |
| EACS  | European AIDS Clinical Society                                                               |
| EMA   | European Medicines Agency                                                                    |
| FDA   | Food and Drug Administration, USA                                                            |
| FOPH  | Federal Office of Public Health's                                                            |
| FTC   | Emtricitabine                                                                                |
| GCP   | Good Clinical Practice                                                                       |
| IB    | Investigator's Brochure                                                                      |
| Ho    | Null hypothesis                                                                              |
| H1    | Alternative hypothesis                                                                       |
| HFG   | Humanforschungsgesetz (Law on human research)                                                |
| HIV   | Human Immunodeficiency Virus                                                                 |
| HMG   | Heilmittelgesetz                                                                             |
| HRA   | Federal Act on Research involving Human Beings                                               |
| HUG   | Geneva University Hospital                                                                   |
| ICH   | International Conference on Harmonisation                                                    |
| IMP   | Investigational Medicinal Product                                                            |

|                  |                                                                                                                                      |
|------------------|--------------------------------------------------------------------------------------------------------------------------------------|
| IIT              | Investigator-initiated Trial                                                                                                         |
| INSTI            | Integrase Strand Transfer Inhibitor                                                                                                  |
| ISO              | International Organisation for Standardisation                                                                                       |
| ITT              | Intention to treat                                                                                                                   |
| KlinV            | Verordnung über klinische Versuche in der Humanforschung ( in English: ClinO, in French OClin )                               |
| LPT h | Loi sur les produits thérapeutiques                                                                                                  |
| LRH              | Loi fédérale relative à la recherche sur l'être humain                                                                               |
| MD               | Medical Device                                                                                                                       |
| NI               | Non-Inferiority                                                                                                                      |
| NNRTI            | Non-nucleoside Reverse Transcriptase Inhibitor                                                                                       |
| NRTI             | Nucleoside Reverse-Transcriptase Inhibitor                                                                                           |
| OClin            | Ordonnance sur les essais cliniques dans le cadre de la recherche sur l'être humain ( in German : KlinV, in English : ClinO ) |
| PCR              | Polymerase Chain Reaction                                                                                                            |
| PBMC             | Peripheral Blood Mononuclear Cells                                                                                                   |
| PI               | Principal Investigator                                                                                                               |
| PP               | Per Protocol                                                                                                                         |
| QALY             | Quality-adjusted life years                                                                                                          |
| RIL              | Rilpivirine                                                                                                                          |
| SAE              | Serious Adverse Event                                                                                                                |
| SDV              | Source Data Verification                                                                                                             |
| SF-12            | Short Form 12-item Questionnaire                                                                                                     |
| SHCS             | Swiss HIV Cohort                                                                                                                     |
| SMT              | Simplified Maintenance Trial                                                                                                         |
| SOP              | Standard Operating Procedure                                                                                                         |
| SPC              | Summary of product characteristics                                                                                                   |
| SUSAR            | Suspected Unexpected Serious Adverse Reaction                                                                                        |
| TLOVR            | Time to Loss of Virological Response                                                                                                 |
| TMF              | Trial Master File                                                                                                                    |
| WHO              | World Health Organization                                                                                                            |
| 3TC              | Lamivudine                                                                                                                           |

## Study schedule

|                                                                    | Screening              | Year 1         |                |                |                |                |                |
|--------------------------------------------------------------------|------------------------|----------------|----------------|----------------|----------------|----------------|----------------|
|                                                                    | -4 weeks to
-1 week | Day 0          | Week 6         | Week 12        | Week 24        | Week 36        | Week 48        |
| Eligibility screen                                     | X                      | X              |                |                |                |                |                |
| Written informed consent                                           | X                      |                |                |                |                |                |                |
| Demographics                                                       | X                      |                |                |                |                |                |                |
| HIV-related data and medical history                   |                        | X              |                |                |                |                |                |
| Concomitant medications                                |                        | X              | X              | X              | X              | X              | X              |
| Full physical examination by physician                 |                        | X              |                |                | X              |                | X              |
| Allocation (double randomization)                                  |                        | X              |                |                |                |                |                |
| Start DTG + FTC OR remain on standard cART                         |                        | X              |                |                |                |                |                |
| Start patient-centered monitoring OR remain on standard monitoring |                        | X              |                |                |                |                |                |
| Adherence check                                                    |                        | X              | X              | X              | X              | X              | X              |
| Adverse events check                                               |                        | X              | X              | X              | X              | X              | X              |
| Drug distribution                                                  |                        | X              | X              | X              | X              | X              | X              |
| HIV-RNA in plasma + sample storage                                 | X          | X β | X β | X β | X β | X β | X β |
| HIV-DNA in plasma (in batch)                                       |                        | X              |                |                |                |                | X              |
| CD4 count*                                                         | X                      |                |                | X*             | X*             | X*             | X              |
| Full blood count*                                                  | X                      |                |                | X*             | X*             | X*             | X              |

Columns with purple background represent visits which need to be performed at study site

 At screening visit: patient chart review for exclusion and inclusion criteria. At day 0: review of laboratory assessments made at the screening visit and completion of the eligibility checklist.

 At day 0: HIV-1 infection, date of HIV-1 diagnosis, years of HIV-1 suppression, nadir CD4 count, zenith HIV-1 RNA, previous genotype, ongoing hepatitis B and C, other co-morbidities. All other visits: updated medical history including changes or additions to diagnoses, diseases and medications will be done in the frame of the concomitant medication and the adverse event check.

 Prohibited: carbamazepine, oxcarbamazepine, phenytoin, phenobarbital, St John's wort and rifampicin.

 Full physical examination by study nurse & medical doctor: vital signs, anthropometric measurements, cardiovascular, respiratory and gastrointestinal systems; central nervous and skin systems as deemed necessary.

 No sample storage on screening visit

|                                                                                                                            |   |   |                                                                                     |     |     |     |   |
|----------------------------------------------------------------------------------------------------------------------------|---|---|-------------------------------------------------------------------------------------|-----|-----|-----|---|
| Safety serum chemistry 6*                                                                                       | X |   | μ                                                                                   | X*μ | X*μ | X*μ | X |
| Urine Beta HCG pregnancy test in women with childbearing potential                                                         | X |   |                                                                                     |     | X   |     | X |
| HIV RNA in plasma and sample storage                                                                                       |   | X | (at any time if HIV-RNA is ≥ 100 copies)                                            |     |     |     |   |
| Genotypic resistance test (real time) and pharmacogenetic analysis (in batch)                                              |   |   | (at any time if HIV-RNA is ≥ 100 copies on two consecutive measurements)            |     |     |     |   |
| DTG and FTC plasma concentration                                                                                           |   |   | (at any time if HIV-RNA is ≥ 100 copies, if twice consecutively only at first time) |     |     |     |   |
| Health-related quality of life questionnaire PROQOL-HIV                                                                    |   | X |                                                                                     | X   |     |     | X |
| Visual analog scale                                                                                                        |   | X |                                                                                     | X   |     |     | X |
| Assess willing for change of monitoring option / satisfaction if patient randomised in the patient-centered monitoring arm |   |   |                                                                                     | X   | X   | X   | X |
| Health related costs assessment                                                                                            |   |   |                                                                                     |     |     |     | X |

 Safety serum chemistry includes CK, creatinine, ASAT, ALAT, gamma-GT, alkaline phosphatases; glucose and lipid profile.

 Patients with HIV-RNA between 20 and 99 copies/ml will benefit from another HIV-RNA measurement after 6 weeks (± 5 days). Patients with HIV-RNA ≥ 100 copies/ml will benefit from another HIV-RNA measurement after 2 weeks (± 5 days).

\* CD4-count, full blood count and safety serum chemistry will be performed on a 3-monthly basis for patients randomized in the standard monitoring arm. Patients randomized in the patient-centered monitoring arm will benefit from these routine tests on a yearly basis (i.e. at day 0 and week 48).

\* Patients new to DTG will benefit from CK measurement and from hepatic safety serum tests, i.e. ASAT, ALAT, gamma-GT, alkaline phosphatases, at week 6 whatever monitoring arm.

† Diabetic patients under concomitant metformine and dolutegravir will benefit from blood glucose and creatinine measurements at weeks 6, 12, 24 and 36 whatever monitoring arm.

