## 5. STUDY OUTCOMES

### 5.1 Primary Outcomes

The *first primary outcome* for the comparison between DTG + FTC dual therapy and standard cART is the proportion of patients maintaining HIV suppression defined as HIV-RNA <100 copies/ml throughout 48 weeks (+/- 21 days). A single blip defined as HIV-RNA <200 copies/ml during the study period is allowed as long as this value is followed by HIV-RNA <50 copies/ml.

The *second primary outcome* for the comparison between patient-centered and standard monitoring is the direct costs of the two study arms from the health care system perspective at week 48.

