## 9.2 Assessments of outcomes

### 9.2.1 Assessment of Primary Outcomes

- Viral load in plasma: HIV-1 RNA level in the plasma will be measured at every study-visit. HIV-1 RNA levels will be quantified using PCR with a limit of detection of 20 copies/ml or less at local virology laboratories. The same assays are being used for and recognised by the SHCS.
- Costs: costs will be measured starting from the baseline visit for the complete study period and from the perspective of the health care provider. Costs will be obtained from health-care insurance of the participants and from trial accounting and collected at week 48. We will consider the following costs:
  - Costs of outpatient medical consultations (HIV and non-HIV medical consultations);
  - Costs of other consultations (non-medical consultations);
  - Costs of antiretroviral drugs;
  - Costs of other drugs;
  - Costs of laboratory tests;
  - Costs of diagnostic tests other than laboratory;
  - Costs of hospitalization;
  - Costs related to the study;
  - Other costs.

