### 11.2 Determination of Sample Size

The first sample size calculation was based on the primary outcome for the comparison between DTG + FTC dual therapy and standard cART, i.e. the comparison between the proportions of patients in the two arms maintaining virologic suppression, using a two-sample proportion test (96). The following assumptions were made:

- Power 80%
- Significance level 0.025 (one-sided Z test of non-inferiority)
- 97% of patients with conventional cART will be virologically suppressed at week 48 (<100 copies/ml)
- 94% of patients on DTG + FTC dual therapy will be virologically suppressed at week 48 (<100 copies/ml)
- Non-inferiority margin of 12% (as in previous non-inferiority trials)(97-104). We chose 12% noninferiority margin because there is no difference in terms of resistance acquisition between 10% and 22% virological failure.

Sample size of 83 patients in each group (total sample size, 166 patients) to achieve 80% power to detect a non-inferiority margin difference between the group proportions of -0.12 was calculated. The power was computed for the case when the actual cART group proportion is 97% and the actual DTG + FTC dual therapy group proportion is 94%. To allow for at least 10% loss to follow-up and also for the randomisation in two steps in this 1:1:1:1 trial, we will aim to recruit **a total of 184 patients**.

The second sample size calculation was based on the primary outcome for the comparison between simplified monitoring and standard monitoring, i.e. the comparison between mean direct costs in the two arms (105). The following assumptions were made:

- Significance level 0.05 (two-sided t-test)
- Direct costs are CHF 25,000 per year (standard deviation (SD) CHF 8,000) with conventional monitoring
- SDs are equal in the two groups (CHF 8,000)

With sample sizes of 92 patients in each group, we will have approximately 55% power to detect a 10% difference in costs, and 99% power to detect a 25% difference in costs. We will also have substantial power to detect small-to-moderate differences in many of the secondary outcomes, e.g. changes in CD4 cell counts or health-related quality of life. The exceptions are rare outcomes such as adverse events, resistance or clinical complications for which the statistical power to detect differences will be low.

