Time to loss of virological response (TLOVR) will be graphically depicted by Kaplan-Meier curves, and evaluated by a univariable and multivariate Cox proportional Hazard model, adjusted for stratified for the type of monitoring and type of treatment.

Predictors of virological failure (nadir CD4 count, baseline HIV-DNA, zenith HIV-RNA, years since HIV infection, years of viral suppression, CD4/CD8 ratio, age, DTG and FTC plasma concentrations, pharmacogenetic analysis, any other relevant clinical or laboratory parameters) will be assessed using forward stepwise multiple logistic regression.

Economic analyses will be performed from the health provider perspective. A multiple linear regression model will be performed to compare the mean direct costs between the two monitoring strategies after adjustment for the treatment arm.

All analyses will be performed in the PP dataset and in the ITT dataset.

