#### **12.1.2 Source data**

Source data must be available at each site to document the existence of the study participants. Source data must include the medical history and treatment of the participant as well as the original documents relating to the study:

- worksheets (as paper CRF) for screening, baseline, week2, week6, week 12, week24, week 36, week 48 visits and extra visit, study drug discontinuation visit and study discontinuation visit);
- logs (adherence log, drug accountability log, adverse event log, concomitant medication log);
- patient diary;
- cost-related letter from the patient's health insurance company.

The following data will be considered as source documents: patient questionnaires, demographic data, visit dates, participation in study and Informed Consent Forms, SAEs, AEs, adherence log, drug accountability log and concomitant medication log. All other data must be available in the participant's hospital chart.

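### The cost comparison is unbiased but less precise than it could cheaply be: no pre-randomisation cost is collected, and drug arm is the only covariate named

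*Protocol*

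**What the plan says.** Section 5.1 defines the second primary outcome as "the direct costs of the two study arms from the health care system perspective at week 48". Section 9.2.1 sets the period, "costs will be measured starting from the baseline visit for the complete study period", and the source: "Costs will be obtained from health-care insurance of the participants and from trial accounting and collected at week 48". The items counted include consultations, antiretroviral and other drugs, laboratory and other diagnostic tests, hospital stays and study-related costs. The row "Health related costs assessment" in the study schedule has one mark, at week 48, and the flow chart in section 9.1 agrees. Section 12.1.2 lists a "cost-related letter from the patient's health insurance company" among the source documents. No section plans a cost for any period before randomisation.

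For the analysis, section 11.4.2 states: "A multiple linear regression model will be performed to compare the mean direct costs between the two monitoring strategies after adjustment for the treatment arm". It names no other covariate. Section 11.2 assumes a mean of CHF 25,000 per year, an SD of CHF 8,000 in both groups and a two-sided t-test at 0.05. With 92 per group it states that "we will have approximately 55% power to detect a 10% difference in costs", and 99% power for a 25% difference.

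**The concern.** The outcome is total direct cost, but monitoring type acts on only part of it: visits, venipuncture, drug delivery and routine tests. Much of the spread between patients comes from features present before entry, such as the antiretroviral regimen and comorbidity. Section 3.1 puts drugs alone for triple therapy at CHF 14,000-22,000 per year, against the assumed mean total of CHF 25,000. For a patient on triple therapy that leaves about CHF 3,000-11,000 for everything else. A 10% difference (CHF 2,500) is already 23-83% of this remainder, and a 25% difference (CHF 6,250) is 57% to more than 200% of it. The smaller difference, where the stated power is low, is therefore the more relevant one.

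Variation that baseline data could explain stays in the error term. A real but modest saving is then easier to miss, and a chance imbalance in expensive patients between the monitoring arms is not corrected.

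**Working it through.** **Inputs.** From section 11.2: n = 92 per monitoring arm, SD = 8,000, difference = 10% of 25,000 = 2,500, two-sided alpha 0.05. From section 3.1: triple-therapy drug cost CHF 14,000-22,000 per year. Assumed, because the protocol gives no value: correlation r between prior-year and trial-year cost, taken as 0.3, 0.5 and 0.7.

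**The plan's own figure.** SE = 8,000 × √(2/92) = 1,179.5. Power = Φ(2,500/1,179.5 − 1.973) = Φ(0.147) = 56%, and the noncentral t gives 55.9%. The stated figure of about 55% is reproduced. For CHF 6,250 the power exceeds 99.9%, in line with the stated 99%. Without a covariate, power reaches 80% at a difference of about CHF 3,305 (13%), or at 2,500 with 161 per arm. Section 11.2 allows for at least 10% loss but does not apply it to the cost calculation; with 83 per arm the power is 52%.

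**Entry-regimen price.** If prices are uniform over 14,000-22,000, their SD is 8,000/√12 = 2,309 and their variance is 5.3 million. That is 5.3/64 = 8% of the variance in the cART arm. If entry price explains nothing in the switched arm, the overall share is half of that, about 4%. Residual SD = 8,000 × √(1 − 0.042) ≈ 7,832, SE = 1,154.7, and power = Φ(2.165 − 1.973) = 57.6%.

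**Prior-year cost, same r in both drug arms.** Residual SD = 8,000 × √(1 − r²).

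**Prior-year cost, r in the cART arm and zero in the switched arm.** With half the patients in each drug arm and a slope per drug arm, the average residual variance is 64 million × (1 − r²/2).

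| r | SD, both arms | Power | 95% CI half-width | SD, cART arm only | Power |
|---|---|---|---|---|---|
| 0 | 8,000 | 56% | CHF 2,327 | 8,000 | 56% |
| 0.3 | 7,632 | 60% | CHF 2,220 | 7,818 | 58% |
| 0.5 | 6,928 | 68% | CHF 2,015 | 7,483 | 62% |
| 0.7 | 5,713 | 84% | CHF 1,662 | 6,951 | 68% |

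Reaching 80% power with 92 per arm needs r of about 0.65 in both drug arms.

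**The case against.** The strongest reply is that nothing here is stated wrongly. Randomisation makes the planned estimate unbiased, its confidence interval already reflects chance imbalance, and the power is disclosed. Section 11.4.6 promises an analysis plan, and covariates are often chosen there. All of this is true. It does not dispose of the point, because section 11.4.2 already states the model and section 9.2.1 the period. An analysis plan can add a covariate, but it cannot supply cost data that were never requested.

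Three stronger readings might be inferred, and the documents do not support them:

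- *That collecting costs once, at week 48, is a defect.* It is not, because that one retrieval covers the whole period from baseline.
- *That the comparison is planned at 55% power without qualification.* That figure belongs to a 10% difference; section 11.2 also gives 99% for 25%.
- *That adjustment would remove the problem.* At r = 0.3, 0.5 or 0.7, 91%, 75% or 51% of the variance remains. Hospital stays that arise during the trial year need not be predicted by earlier cost.

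Two practical objections also stand. Half the patients change regimen by design, and antiretrovirals make up 56-88% of the assumed mean (14,000/25,000 to 22,000/25,000), so prior cost may predict poorly in that half. In addition, version 5.1 is dated 30 July 2019, after the planned end of recruitment (June 2018) and of the study period (May 2019). A prior-year request could therefore need renewed consent, and the protocol does not describe what the insurer letter contains.

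**Conclusion.** The point holds as a matter of efficiency, not validity. The cost comparison is unbiased, and its stated power is correct for the stated inputs. It leaves out an adjustment that needs no new data and another that uses a source already being approached.

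The gain from entry-regimen price is small: about 4% of variance overall and about 2 points of power. That rests on a uniform price distribution, and on the triple-therapy range also fitting the eligible PI-based dual regimens, which may fall outside it. The gain from prior-year cost depends on a correlation that the protocol does not give. Over r = 0.3 to 0.7, power for CHF 2,500 lies between about 58% and 84%, and the top of that range requires the correlation to hold equally in patients who switch regimen. Adjustment would reduce variance and chance imbalance between the monitoring arms without eliminating either.

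**What to change.** 1. In section 11.4.2, add the price of the regimen at entry as a baseline covariate in the cost model, with its interaction with drug arm. Every patient's entry regimen is established at eligibility, so this costs only wording. State how PI-based dual regimens are priced.
2. In section 9.2.1, extend the existing insurer request to the 12 months before Day 0 and use that cost as a covariate. Let its slope differ by drug arm, and include a missing-value indicator where the insurer does not reply. The cost is one more period on the request, consent wording (possibly renewed consent, given the stage of the trial) and some non-response.
3. Keep the model adjusted only for drug arm as a supportive result.

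Fix the covariates before any cost data are compared by monitoring arm. If consent for prior-year data cannot be obtained, item 1 can still be done alone, with its smaller gain.
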